### Implementation {16c}

The drawing of the participants takes place during the initial appointment for the informed consent. Since the participants come continuously and from all over Lower Austria, interviews are conducted both in person and via video calls. In order to make the ballot box drawing online and offline comparable, a computer-based drawing will take place in both cases, i.e., similar to a memory game. The test persons turn over one (of 196) cards and thus find out in which group they participate and, at the same time, receive their ID for the study. The drawing takes place without putting the cards back.

The maximum group size is 14 participants. When an intervention or control group is full, the recruitment of the next group will be started. The ID numbers are therefore not consecutive within the groups, but random. There is no upper limit regarding the number of participants for the first recruitment date.

## Assignment of interventions: blinding

### Who will be blinded {17a}

Blinding of trial participants will not be possible because of the obvious differences between the intervention group and the control group. Blinding will be implemented for the medical staff and the outcome assessors of the measurements and the following analyses (see {19}).

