### Who will take informed consent? {26a}

Interested participants can register using an online registration form and a central study staff member - a dietitian or a nutritionist - will contact them afterwards.

During the initial appointment, which will be conducted online via MS Teams or face to face at the St. Pölten University of Applied Sciences, the staff member will explain the trial (background, protocol, different roles, importance of randomization and adherence) to potential participants and will review the consent form. Furthermore, the staff member will answer any questions arising. When the trial and its requirements are understood completely, the informed consent form will be signed by the participant. This can be done via electronic or handwritten signature.

All eligible participants must complete the consent procedure before enrolment and randomization. There are separate consent forms for general participants and for moderators.

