### Intervention description {11a}

The intervention is developed and conducted by an interdisciplinary team. Dietitians and moderators play an active role in the operational process of the intervention.

Dietitians are part of the team that develops the training curricula and is responsible for the training of the moderators and participants. They will supervise all moderators once a month via online meetings. During these meetings, the dietitians support moderators, e.g., if specific knowledge concerning diabetes care is needed or in case of technical problems.

Moderators act as facilitators and coordinators but they do not give medical or disease-related advice. In order to moderate communication and exchange in the IMS group effectively and authentically, personal and practical disease-related experiences of the moderator and the readiness to share these experiences with the group are essential. Moderators receive 9 h of training on the content to be shared via IMS and communication strategies to facilitate group exchange, peer support and behavioral change.

Participation in the clinical trial will last 15 months (1 month training/first measurement, 7 months intervention, 7 months follow-up). 196 participants will be randomly assigned to one of two groups: the intervention group or the control group. Participants who are randomly assigned to the intervention group will attend a 2 h technical training in connection with the first measurement. In the course of this training, they will learn how to use the *mattermost* app. After this training, they will join a *mattermost* group (instant messaging service group) with a maximum of 14 people for 14 months (7 months guided and seven without guidance). For the first 7 months of the intervention, an empowerment-based IMS communication strategy for diabetes self-management peer support has been developed.

Moderators are provided with a detailed handbook on web-based diabetes-related content and communication strategies to share this content with the group.

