### Strategies to improve adherence to interventions {11c}

The intervention consists of a peer-supported IMS intervention in addition to standard therapy. Therefore, adherence of participants to the IMS intervention pertains mainly to the IMS strategy, the measurements, and the initial training sessions.

The first step to improve adherence is the holistic explanation of the trial to interested participants during the initial appointment [50, 51]. In this appointment, sufficient time is scheduled in order to enable comprehensive understanding concerning the trial among participants.

Those who have greater responsibility - the moderators - will be individuals participating in the disease management program “Therapie aktiv – Diabetes im Griff” (https://www.therapie-aktiv.at), which is provided by the Austrian Health Insurance Fund. Hence, they are already proven to be generally adherent and engaged in their disease management. These moderators will positively influence their group members through the role model effect.

A dietitian experienced in counseling will support the moderators if problems arise and they will supervise all moderators once a month via online meetings. During the supervision, the dietitian will reflect on the past month and discuss the next steps of the IMS strategy with the moderators. If necessary, the communication expert can provide further assistance during these meetings.

Furthermore, we expect an additional positive social effect: participants will identify with their *mattermost* group and, in the next step, with the DiabPeerS trial. Hence, they will be interested in a successful intervention and participate actively. Also, frequent personal contact between the central study staff (EH, MH, AEZ) and the participants throughout the whole trial (initial appointment, four measurements, supervision meetings) will support adherence [50].

The IMS strategy (see {11a}), the core element of this trial, aims to improve diabetes self-management. Taking into consideration that regular medical appointments and monitoring are central in diabetes self-management, we assume that this increasing competence will support adherence to intervention as well.

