Additionally, clinical visits will be designed as conveniently for the participants as possible [50, 51]. The participants will have easy access to the locations of training sessions and measurements: they can choose one out of four central locations in Lower Austria for their measurements. These locations are well known and easily accessible: the St. Pölten University of Applied Sciences and hospitals in Wr. Neustadt, Hollabrunn, and Mauer/Amstetten. These locations are equally distributed over Lower Austria from a geographical point of view and can be reached comfortably by car as well as public transport. The training sessions for the participants will take place after the first measurement at the same location. The training sessions for the moderators will be held at the St. Pölten University of Applied Sciences. Therefore, only individuals from St. Pölten or the surrounding areas are eligible to become moderators. If a participant misses one measurement, it is possible to make a new appointment within a certain timeframe.

Furthermore, study staff will call participants to schedule visits and send them reminders via SMS and e-mail 48 h before the appointment. During each measurement, participants and moderators will have the opportunity to discuss their results, such as body composition, with an experienced dietitian, which is not very common in Austria and will increase engagement [50].

Additionally, participants and moderators will receive a financial compensation of 50 EUR and a small gift after the last measurement.

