### Procedure for unblinding if needed {17b}

It is an open-label study and therefore unblinding will not occur.

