## Data collection and management

### Plans for assessment and collection of outcomes {18a}

During the online registration, contact data of all interested individuals will be collected. The data will be deleted if the person disagrees to participate in the trial.

All parameters as described in the subsection “Outcomes (see {12})” will be taken in a group testing setting with appropriate Coronavirus SARS-CoV-2 (COVID-19) safety measures, e.g., testing, vaccination, hygiene procedures by the staff of the St. Pölten University of Applied Sciences either at the university itself or at the Landesklinikum Wr. Neustadt, Hollabrunn, or Mauer/Amstetten.

The measurements will take place in the morning in a fasting state and with anthropometric measurements with light clothing. Anthropometric measurements will be conducted by dietitians. Blood pressure and blood samples will be taken by nurses. Fresh blood samples will be taken by the staff of the St. Pölten University of Applied Sciences, centrifuged within a timeframe of twenty minutes, and analyzed within a timeframe of 3 h maximum after the centrifugation by the University Hospital St. Pölten. The laboratory of the University Hospital St. Pölten is ISO 9001-certified and will handle all samples according to its quality management.

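### Outcome assessors are stated to be blinded, but the protocol's own staff roles and ID code do not secure it; dietitian-taped waist circumference is the main exposure

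*Protocol article*

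**What the plan says.** All references are to the protocol article.

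- **Blinding claim.** {17a} accepts that participants cannot be blinded and then states: "Blinding will be implemented for the medical staff and the outcome assessors of the measurements and the following analyses". It refers to Data management {19}. There, the stated mechanism is the identification code marked on the questionnaires, which is said to keep study staff from knowing a participant's group.
- **Label.** {17b} adds: "It is an open-label study and therefore unblinding will not occur".
- **Who holds the initial appointment.** Under {26a}, after online registration, "a central study staff member - a dietitian or a nutritionist - will contact them afterwards", and that staff member conducts the appointment.
- **When allocation becomes known.** {16c}: "The drawing of the participants takes place during the initial appointment for the informed consent". The card turned over shows both the group and the study ID.
- **Continuity of staff.** {11c} lists three central staff members and describes their contact with "participants throughout the whole trial (initial appointment, four measurements, supervision meetings) will support adherence".
- **Dietitians' intervention roles.** Under {11a}, dietitians belong to the team that trains moderators and participants. Of the moderators it says: "They will supervise all moderators once a month via online meetings". Only the intervention arm receives the 2 h app training, and {11c} says: "The training sessions for the participants will take place after the first measurement at the same location".
- **Dietitians' measurement role.** {18a}: "Anthropometric measurements will be conducted by dietitians". Nurses take blood pressure and blood.

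**The concern.** A trial can be open to participants and still have blinded assessors, so the open-label wording in {17b} is not in itself the problem. The problem is that {17a} asserts blinding for the measurements in general. Elsewhere the article places the same staff group, and in part the same listed individuals, both where allocation becomes known and where outcomes are measured. The one safeguard it names, the ID code, is described in two incompatible ways.

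At stake is what the trial may claim. Readers judge risk of bias by whether assessors were blinded. As written, every measurement would be reported as assessor-blinded, including one hand-taken measurement for which the article does not support that description.

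**Working it through.** No figure in the plan bears on this point, so there is nothing to recompute. The check sets the sections side by side.

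For {17a} to hold, two conditions are needed: (a) the people who measure have no other task that reveals allocation, and (b) the ID they see does not reveal the group.

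**Condition (a): roles**

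| Staff | Task that can reveal allocation | Presence at measurements |
|---|---|---|
| Central staff (dietitian or nutritionist) | Hold the appointment at which the card shows group and ID ({26a}, {16c}) | Contact with participants at all four ({11c}) |
| Study coordinator | Keeps the code key; has access to the exported chat data ({19}) | Takes part in every measurement, organising participants and codes ({19}) |
| A second central staff member | Has access to the exported chat data ({19}); one of those who check it weekly ({21a}) | Among those listed in {11c} for the four measurements |
| Dietitians | Belong to the training team; supervise the moderators monthly ({11a}) | Take the anthropometry ({18a}) |
| Nurses | None stated | Take blood pressure and blood ({18a}) |

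Chat data exist only for the intervention arm and include who posted ({12}), so access to them identifies members of that arm. For the central staff and the coordinator, the overlap of allocation knowledge with presence at measurements is stated in the text. For the dietitian holding the tape it is likely but not stated: no section says that the measuring dietitian is one who held the appointment, trained or supervised.

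**Condition (b): the code**

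- {16c} says IDs come with the cards and are random within groups.
- {19} first says that coding is by consecutive numbers, from which the group, though not the identity, can be inferred.
- {19} later says that the code keeps study staff from knowing the group.

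The two statements in {19} cannot both be true. Even a code that shows nothing would not blind someone who saw group and ID on the same card.

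**Timing**

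Only participants already assigned to the intervention arm attend the training linked to the first measurement, so the draw precedes T0. Knowledge from the draw could therefore touch T0 to T3. Knowledge from the training, which follows the first measurement, could touch only T1 to T3.

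**Outcomes exposed** ({12}, {18a})

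| Outcome | How obtained | Exposure to assessor knowledge |
|---|---|---|
| HbA1c (primary), glucose, lipids | Hospital laboratory | Little |
| Weight, height, body fat | One device | Little |
| Blood pressure | Device, taken by nurses | Little; nurses have no stated allocation role |
| Questionnaires | Self-report by unblinded participants | Unblinded whoever the staff are |
| Waist circumference and waist-to-height ratio | Tape; anthropometry is assigned to dietitians | Exposed |

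**The case against.** The strongest reply is that overlap of professions is not overlap of persons. Several dietitians may be involved, and the one who measures need not have seen the draw or taught the group. {11c} speaks of personal contact at the measurements, not of measuring. {19} gives the coordinator an organising role there, and participants turn the cards themselves. Rostering is detail that a condensed article may leave to the full protocol. Results discussion with a dietitian is offered to everyone after measurement. The primary outcome is a laboratory value, and none of H1 to H5 concerns waist.

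Much of this stands, and it rules out three stronger readings that a reader might infer:

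- **That all assessor-dependent outcomes are taken unblinded.** The documents do not show this. Nurses have no stated allocation role, most readings come from a device or laboratory, and the identity of the measuring dietitian is not given.
- **That dietitians who know the arm would shift HbA1c through their feedback.** The documents offer the discussion to both arms and describe no difference. Differential advice would be a co-intervention question, not one of blinded measurement.
- **That the bias can be expressed as a share of the effect the trial is sized for.** The documents give neither a standard deviation for waist nor any basis for the size of a reading bias, and the effect size in {14} was assumed for HbA1c.

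What does not stand is the appeal to missing detail. {17a} makes a positive claim, {11c} places listed allocation-aware staff at every measurement, and {19} contradicts itself about the code. These are conflicts in the text shown, not gaps that a roster would fill.

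**Conclusion.** The point holds in a limited form: blinding of outcome assessors is asserted, but the stated roles and code do not secure it. The exposure is mainly one hand-taken secondary measurement, waist circumference, and the ratio derived from it. The analysis of HbA1c is little affected. The size of any bias cannot be estimated from the documents.

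The conclusion assumes that staff holding the initial appointment can see or learn the card drawn; the article states no arrangement to prevent it. It does not depend on showing that any particular dietitian was unblinded. The point is worth acting on because it concerns a design property that the trial would report, and the correction is small.

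**What to change.** 1. State in {17a} and {18a} that waist and the other anthropometry at T0 to T3 are taken by existing staff who have no part in the draw, participant training, moderator supervision or chat review. These could be the nurses already present or a dietitian kept apart from those tasks.
2. Use an ID code that does not reveal the group, and reconcile the two statements in {19} with each other and with the card IDs in {16c}.
3. If the roles cannot be separated, restrict {17a} to laboratory outcomes and genuinely separate staff, and do not report anthropometry as assessor-blinded.

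The cost is a few sentences of text and somewhat less freedom in rostering, plus some nurse time if nurses take the tape measurement. The documents give no staffing figures from which to quantify this. No extra visits or participants are needed.

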The posts will be evaluated by content analysis to explain and interpret the results of (H2) diabetes self-management behaviors, (H3) quality of life of participants, and (H4) medication adherence of participants. The codebook will be developed in collaboration with medical professionals for the coding of adherence and non-adherence behaviors. The quantified data will then be made available for the in-depth analysis of questionnaire data and medical scores.

According to past research [65–67], personality traits such as extraversion can influence our communication behavior: extraverted individuals speak more often, make more eye contact, smile, and nod more frequently than introverted persons. (H5) Therefore, we assume that extraversion will correlate positively with the number of posts as well as the number of reactions and emojis to posts from others.

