### Data management {19}

The participants agree that for the purpose and in the course of this study, the St. Pölten University of Applied Sciences will collect and process the following personal data: name, age, gender, education, income, occupational situation, housing situation, migration background, personality characteristics, clinical information such as age at diabetes diagnosis, social support, self-efficacy, depression, quality of life, diabetes knowledge, treatment adherence, diet and exercise behavior, nicotine and alcohol consumption, diabetes self-management, medical consultations during the last 6 months, HbA_1c_, fasting glucose, total cholesterol, HDL, LDL, triglycerides, blood pressure, body weight and height, waist circumference, and body composition.

Furthermore, the participants agree that the University Hospital St. Pölten may transmit the following data in indirectly personalized (pseudonymized or encrypted) form to the St. Pölten University of Applied Sciences for the purpose of analyzing whether the intervention is effective with regard to the defined parameters compared to conventional therapy: HbA_1c_, fasting glucose, total cholesterol, HDL, LDL, triglycerides.

The participants’ data will be pseudonymized and assigned a fixed identification code. This code will be stored safely in a password-protected file, accessible only by the study coordinator (EH) and central staff members (UH, AEZ). The key for the coding is kept separately and inaccessibly by the study coordinator. Thus, it is only possible for persons who are entrusted with the evaluation of the data to infer the identity of the participants.

Data acquisition and data processing are performed using commercial software. All data obtained are stored in computer files in encrypted form. The coding is done by means of consecutive numbering, from which only the allocation to the corresponding group, but in no case a conclusion as to the identity of the participant is possible.

Data will be stored and analyzed via the statistical software package SPSS at servers of the St. Pölten University of Applied Sciences, only used for this special study and not be passed on to third parties. The handling of the data complies with the European General Data Protection Regulation, the Austrian Data Protection Act, and the recommendations of the Ethics Committee of Lower Austria.

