To be able to merge the data from the paper-and-pencil questionnaires, anthropometric measurements, and blood pressure data, a defined coding system will be used. Therefore, the study coordinator will take part in every measurement and organize the participants and coding system. Hence, every participant will get his or her identification code and the questionnaires will be marked with this code at the beginning of each measurement. The identification code ensures that the study staff do not know to which group each participant belongs. Paper-and-pencil questionnaires will be checked by the study staff in terms of completeness and correctness related to the specifications of the questionnaires. These data will be transferred into SPSS manually and controlled by another member of the study team. Results of the biochemical analysis will be mailed via encrypted Excel files from the University Hospital St. Pölten to the St. Pölten University of Applied Sciences and imported into SPSS by the study coordinator. Blood samples will be disposed of and Excel files will be deleted after integration into SPSS. Furthermore, the St. Pölten University of Applied Sciences performs data back-ups on a daily basis. All signed informed consent forms as well as all collected paper-and-pencil sheets will be stored in a locked place, accessible only to the study coordinator and a central staff member (UH). All data will be stored at the St. Pölten University of Applied Sciences for ten years after the study’s end. After that, all data will be destroyed.

To ensure data quality, the study coordinator will control the data regularly including checking the range of values or double data entry.

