Data protection concerning the instant messaging tool will be met by using the instant messaging communication tool *mattermost* (https://mattermost.com/). *mattermost* has been chosen for its clear terms and conditions and data handling strategy. The open-source software *mattermost* was chosen because it can be operated securely and privately, as we will run it on-premise and not as a cloud solution. *mattermost* will be hosted as a software solution in an ISO 27001:2013 certified data center in Vienna for the duration of the project. *mattermost* provides a holistic messaging solution that allows to communicate securely and efficiently via 1:1 and group messaging, meeting, and file sharing as well as audio/video integrations. The data export based on Docker is conducted in the Viennese data center and made available only to selected members of the study team (EH, AEZ, JG). The data are cleaned, and unstructured communication data will be structured using content analysis and MAXQDA (see {12}). Subsequently, these data will be pseudonymized and transferred into SPSS for further analysis.

Results of all analyses will be reported in an aggregated and strictly anonymous form.

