### Confidentiality {27}

All collected data will be kept confidential as described in “Data management” (see {19}). Only the study coordinator and central staff members (UH, AEZ) can open the password-protected file to link personal information and code. The final pseudonymized dataset in SPSS will be used by the study staff for analyses, publications, and reports only for this study.

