### Methods for additional analyses (e.g., subgroup analyses) {20b}

As we want to assess the association between specific personality traits and the benefits of peer-supported IMS, we use validated and published questionnaires, which we repeatedly distribute to all experimental and control groups at different times of the study.

In addition to the observed communication behavior, we use the information from the questionnaires (see {12}) to test the hypotheses and in particular related to (H2) diabetes self-management behaviors, (H3) quality of life of participants, and (H4) medication adherence as well as (H5) the level of extraversion.

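### The protocol says the ID code keeps the analyses blinded, but the data handling it describes does not deliver this for the data analysis

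*Protocol article*

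**What the plan says.** - **Blinding promised.** Who will be blinded {17a}: "Blinding will be implemented for the medical staff and the outcome assessors of the measurements and the following analyses", with a reference to Data management {19}. Procedure for unblinding {17b} calls the trial open-label.
- **Means.** Data management {19}: "The identification code ensures that the study staff do not know to which group each participant belongs".
- **ID code.** An earlier paragraph of {19} says that numbering is consecutive and that group allocation, though not identity, can be read from it. Implementation {16c} says the ID numbers are random and not consecutive within groups.
- **Chat data.** Intervention description {11a} keeps controls out of any messenger group. On the exported and coded chat data, {19} says "Subsequently, these data will be pseudonymized and transferred into SPSS for further analysis", and Outcomes {12} says "The quantified data will then be made available for the in-depth analysis of questionnaire data and medical scores".
- **Dataset.** Confidentiality {27}: "The final pseudonymized dataset in SPSS will be used by the study staff for analyses, publications, and reports only for this study".
- **Staff.** {19} gives the code file to the study coordinator and two central staff members, and the chat exports to the coordinator, one of those two, and a third team member. The section on the data monitoring committee {21a} has the last two check the chat protocols weekly. {11b} says these weekly reviews keep the coordinator and selected team members informed.

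**The concern.** The protocol claims a protection and names the device that provides it. Two things in the same section undo that device: a code that shows the group, and variables that can be filled for one arm only. Once the second is linked to outcomes, even a perfectly neutral ID cannot hide the arm.

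This matters because the article leaves some analysis decisions to be made on the data. Statistical methods {20a} chooses between repeated measures ANCOVA and rank-based tests after looking at histograms, skewness and kurtosis. HbA1c is measured at three visits after baseline. Questionnaire scales with at least 80% of items answered are completed by a nearest neighbor method. Readers told that the analyses were blinded will assume that such choices were made without knowledge of the arms. As described, nothing secures that.

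**Working it through.** The plan gives no figure on this point, so the check sets its statements side by side.

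**1. Does the promise reach the data analysis?** The wording of {17a} could be confined to laboratory analyses. But it refers to {19}, which covers SPSS storage, coding and analysis, and "The identification code ensures that the study staff do not know to which group each participant belongs" speaks of study staff in general. The wider reading is the better supported one, though not the only one.

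**2. Does the ID code hide the arm?** According to {16c} and the later paragraph of {19}, yes. According to the earlier paragraph of {19}, no, because allocation can be read from the number. These cannot all be true of one code. If the group meant is the messenger group of 14 and not the arm, belonging to one still shows the intervention arm.

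**3. Do chat variables show the arm?** The intervention arm has 98 participants (7 groups × 14 = 98) and the control arm 98. Only the first 98 can have posts, reactions or content codes. In a linked file:
- any row with a recorded post belongs to the intervention arm;
- an intervention participant who never posts is recognisable only if zero is coded differently from missing.

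Masking the arms as A and B would not help, since the group with chat data is plainly the intervention.

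**4. Are they linked to outcomes?** Yes, at some stage. Outcomes {12} uses the coded posts to explain the results for H2, H3 and H4. Methods for additional analyses {20b} says "In addition to the observed communication behavior, we use the information from the questionnaires", naming H2 to H5 in particular. H5, as stated under Objectives {7}, relates extraversion to benefit measured by messenger use, quality of life and HbA1c.

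**5. Are they there when H1 to H4 are tested?** Not stated. {19} says only that chat data go into SPSS, not into which file or when. A single file is suggested by the singular noun in {27}. For H2 to H4 the link is explicit but its timing is not. H1 is not named in the chat-linked work of {12} or {20b}.

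**6. Who knows the arms regardless of SPSS?** One central staff member holds the code file, receives the exports and reviews the chats weekly. The coordinator holds the code file and receives the exports. A third member receives the exports and reviews the chats. Anyone reading a group's chat knows that its members are in the intervention arm. {19} adds that "it is only possible for persons who are entrusted with the evaluation of the data to infer the identity of the participants". That concerns identity, not arm, but an evaluator who can identify a participant and also reads the chats knows that participant's arm.

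**The case against.** The strongest reply is that merge order, masked labels and syntax lock belong in an analysis plan or data management plan, neither of which is shown, and that this is a condensed article. That stands as far as silence goes: the absence of a merge rule is not in itself a fault. It does not remove the conflict between a blinding claim and the handling described in the section cited to support it, nor the contradictory accounts of the ID code.

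A second reply is that {17a} may mean laboratory analyses only. That is possible. If so, {17a} and the sentence on study staff need rewording.

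Two stronger readings are tempting and should be resisted. A reader might infer that each participant's arm is visible during all the H1 to H4 comparisons. The documents do not say so: a blinded comparison before the merge is not excluded, H1 is not named in the chat-linked sections, and silent participants may not be recognisable. A reader might also attach an inflated false-positive rate, obtained by letting the analyst take the smallest p-value over tests and visits. That would measure freedom of choice, not arm visibility. Two-sided ANCOVA and Mann-Whitney p-values are unchanged when the arm labels are swapped, so an analyst seeing only A and B could select just as freely.

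Finally, HbA1c is an instrument reading from a hospital laboratory, and nothing suggests that the laboratory sees chat data. That stands: the point concerns the data analysis, not the measurement of the primary outcome.

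**Conclusion.** The concern holds in a limited form. The protocol says that the analyses are blinded and that the ID code keeps study staff from knowing the group, but the handling it describes does not deliver this for the data analysis. The firmest evidence is the contradiction about the code, together with the fact that staff with the code file or the exports also read the chats. Exposure through chat variables is likely, is best supported for H2 to H4, and is an inference for H1.

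This rests on reading {17a} to include data analysis and on the single dataset suggested by {27}. The documents allow no numerical size. The consequence is that choices made on the data lack the protection claimed for them. The point should be settled before analysis.

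**What to change.** 1. Reconcile the statements on the ID code in {16c} and in both paragraphs of {19}, so that one account says whether the number shows the group.
2. Prepare an H1 to H4 file without chat variables, with an ID from which the arm cannot be read and with the arm codes shuffled. Shuffling is needed, not just A/B labels, because real groups under masked labels still show the result of each test.
3. On that file settle the distribution checks, the tests and the SPSS syntax, and lock them with a date.
4. Attach the true arms and run the locked syntax.
5. Only then merge chat counts and content codes for H5 and the explanatory analyses.
6. Reword {17a} to say who is blinded and who is not. Staff who read the chats cannot be blinded to the intervention arm, and delaying the merge does not change that. Alternatively, state that the data analysis is unblinded.

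The cost is one extra export, a sequencing rule and a slightly later start for the chat-based analyses. No additional participants or staff are needed.
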